| Monitoring    | Wireless remote vital signs, telemetry, activity tracking, sleep tracking, predictive analytics for deterioration                                                                                                                                                                                                                                                                                                                                                                                                                                                                                                                                                                                                                             |

As denoted in the figure above, the physician will make at least one daily interaction with the patient. The nature of this interaction will be guided by the control versus intervention arm, and the physician's discretion. If the patient is in the control arm, the physician will make a daily in-person visit (usual care). If the patient is in the intervention arm, the physician sees the patient remotely via facilitated video, including near-real-time transmission of heart, lung, and abdominal sounds as needed. The nurse or paramedic seeing the patient will facilitate a physical exam and discussion with the patient. If the physician chooses for clinical purposes, s/he may still see the patient in-person. At the discretion of the physician, paramedic, and nurse, the physician can make additional visits should the patient's clinical condition require it. The nurse or paramedic will make at least two daily visits to the patient's home. At the discretion of the physician, paramedic, and nurse, the nurse or paramedic can make additional visits should the patient's clinical condition require it. This will be an ongoing twice daily discussion among clinicians, patient, and caregivers, as applicable.

As denoted in the figure above, a patient or clinician can initiate a video or in-person visit at any time.

As denoted in the figure above, a home health aide may be deployed. If deemed necessary by the home hospital attending, patient, and/or caregivers, the home hospital program can provide an on-demand home health aide that can provide care in 12 hour shifts.

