As denoted in the figure above, the home hospital team uses a suite of communication software to communicate with the patient and among team members. The home hospital team has the option of using a home hospital dashboard that combines a patient list with communication (video, text) and visualization of data from monitoring devices (VitalPatch, for example). Clinician-facing tools: patient list, communication (video, text, audio), and visualization of and alerting on data from monitoring devices (VitalPatch, for example). Patient-facing tools: plan for the day, calendar for the day, reminder

from the care team, a simple snapshot of sleep and activity, and the ability to contact the care team via video, text, or audio . Caregiver-facing tools: same as patient-facing tools, if permission is granted by the patient or health care proxy.

For patients with chronic/stable dementia, they will receive mental status assessments (eg, Confusion Assessment Method) by the home hospital RN or paramedic at each visit (at least 2 daily). As is standard of care, we will take measures to avoid delirium: open blinds to allow light in during the day, minimize environmental noise, encourage typical routines to optimize eating and sleeping, and reassess medication list for culprit medications.

Clinical parameters measured will be at the discretion of the physician, paramedic, and nurse, who treat the participant following evidence-based practice guidelines, just as in the usual care setting. Monitoring and data collection will be performed by home hospital clinicians. The clinical home hospital team manually checks vital signs at least twice daily. If deemed necessary based on a patient's acuity, the home hospital team can visit additional times during the day and a dedicated overnight aide can be deployed to check vital signs multiple times throughout the night. At all times, the patient and care team have 24/7 access to the home hospital attending physician, who can be in the patient's home in less than 20 minutes at any time of day. On top of this "on-the-ground" team, the home hospital attending is notified with an alarm should there be delayed data transfer. Such an alarm would cause the attending to contact the patient as deemed clinically appropriate. Please see below for all collected data points.

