### Safety

| Measure | Source                                                       | Day(s) Obtained |
|---------|--------------------------------------------------------------|-----------------|
| Fall    | RA via MD/RN for home patients; MD EHR review for inpatients | Daily           |

|                                        |                                                                                                                                                                                 |           |
|----------------------------------------|---------------------------------------------------------------------------------------------------------------------------------------------------------------------------------|-----------|
| Delirium, y/n and time to resolution   | RNs in home and inpatient settings calculate the CAM (standard of care in both). RA will obtain the home patient CAM via the home RN; RA will obtain the inpatient CAM via EHR. | Daily     |
| Potentially preventable VTE            | RA via MD/RN for home patients; MD EHR review for inpatients                                                                                                                    | Daily     |
| New pressure ulcer                     | As above.                                                                                                                                                                       | Daily     |
| Thrombophlebitis at peripheral IV site | As above.                                                                                                                                                                       | Daily     |
| Hospital Acquired Condition     |                                                                                                                                                                                 |           |
| CAUTI                                  | As above.                                                                                                                                                                       | Daily     |
| Clostridium difficile                  | As above.                                                                                                                                                                       | Daily     |

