| MRSA                                   | As above.                                                                                                                                                                       | Daily     |
| Transfer back to hospital a | RA via MD/RN                                                                                                                                                                    | Discharge |
| All-cause mortality during admission   | RA via MD/RN for home patients; MD EHR review for inpatients                                                                                                                    | Discharge |
| Unplanned mortality during admission   | RA via MD/RN for home patients; MD EHR review for inpatients                                                                                                                    | Discharge |
| All-cause 30-day mortality             | RA via pt/caregiver call                                                                                                                                                        | +30       |
| Unplanned 30-day mortality             | RA via pt/caregiver call                                                                                                                                                        | +30       |
| Heart Failure                   |                                                                                                                                                                                 |           |
| New arrhythmia                         | RA via MD/RN for home patients; MD EHR review for inpatients                                                                                                                    | Daily     |
| Hypokalemia                            | As above.                                                                                                                                                                       | Daily     |
| Acute kidney injury                    | As above.                                                                                                                                                                       | Daily     |

a: intervention arm only

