| Paramedic + nurse care vs nurse care alone              | Retrospective, non-inferiority, propensity-weighted evaluation               | Number of adverse events                              | Unplanned readmission after index, y/n
Picker experience questionnaire
Global experience score
Personnel costs           |

\*Non-inferiority for this outcome

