### *Remote vs In-Person Physician Care*

In a randomized controlled non-inferiority trial, we will test an in-person daily physician visit (“in-person care;” control) vs a daily physician visit conducted remotely via video facilitated by a care team member (“remote care;” intervention) for acutely ill patients who are home hospitalized. The primary outcome (dependent variable) is number of adverse events during the acute episode of care (see “Summarizing Adverse Events” table below). The primary predictor (independent variable) is study arm (in-person care vs remote care). We will assess the non-inferiority of the primary outcome with a generalized linear model using Poisson distribution, given the primary outcome is count data. Although we have multiple covariates of interest, we are cognizant of over adjustment. We plan to adjust for age, gender, race/ethnicity, PRISMA-7, education, and HOSPITAL score). We may include additional covariates if groups have significant differences at baseline.

Because patients in the intervention arm will receive at least some of their intervention through a “change agent” (in this case, a Home Hospital team) shared with other participants, we need to account for this in the analysis. We will therefore cluster by Home Hospital physician using general estimating equations.

Other outcomes will be analyzed in a similar manner, using Poisson regression for other “count” outcomes (e.g., number of new or worsening signs or symptoms per patient, days at home since discharge), multivariable logistic regression for binary outcomes (e.g., 30-day readmission, ED visit, PCP

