#### Summarizing Adverse Events

| Measure                                     |
|---------------------------------------------|
| Fall                                        |
| Delirium                                    |
| Potentially preventable VTE                 |
| New pressure ulcer                          |
| Thrombophlebitis at peripheral IV site      |
| CAUTI                                       |
| New Clostridium difficile                   |
| New MRSA                                    |
| New arrhythmia                              |
| Hypokalemia                                 |
| Acute kidney injury                         |
| Transfer back to hospital                   |
| Mortality (unplanned) during admission      |
| Mortality (unplanned) 30-day post-discharge |

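### Remote vs in-person trial: most adverse events are reported via the MD and RN, but the MD sees the patient at the bedside daily in the control arm only, and no arm-independent ascertainment is fixed

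*Protocol*

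**What the plan says.** The section Remote vs In-Person Physician Care defines the endpoint of the non-inferiority trial: "The primary outcome (dependent variable) is number of adverse events during the acute episode of care". The components are listed under Summarizing Adverse Events.

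The Safety table fixes how each component reaches the research assistant (RA):

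- Falls, VTE, pressure ulcer, thrombophlebitis, the hospital-acquired infections, arrhythmia, hypokalemia and kidney injury: "RA via MD/RN for home patients; MD EHR review for inpatients", directly or by reference to that row.
- Delirium: "RA will obtain the home patient CAM via the home RN".
- Transfer back to hospital and death during admission: also through the MD or RN.
- 30-day mortality: "RA via pt/caregiver call". The adverse-event list includes it as "Mortality (unplanned) 30-day post-discharge".

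Study visits and measured parameters sets the contacts. The control-arm physician visits in person every day. The remote-arm physician uses facilitated video and may choose to attend in person. For both arms, "The nurse or paramedic will make at least two daily visits to the patient's home", and in the remote arm the nurse or paramedic facilitates the physical exam. For patients with chronic or stable dementia, "they will receive mental status assessments (eg, Confusion Assessment Method) by the home hospital RN or paramedic at each visit".

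Under Safety monitoring, a blinded committee judges whether certain events are attributable to the intervention. The types are fall, medication error, DVT/PE, death during admission and transfer back.

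The Study endpoints table also lists "Paramedic + nurse care vs nurse care alone", a retrospective non-inferiority comparison with the number of adverse events as its primary endpoint.

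**The concern.** In a non-inferiority trial, events missed in the experimental arm move the result toward the conclusion the trial hopes to reach. Here one of the two named informants is the physician whose daily bedside visit is the randomised factor. The informants are treating clinicians who know the arm. The components most exposed are those that have to be noticed at the bedside: delirium, pressure ulcer, thrombophlebitis and falls.

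The committee cannot recover an event that nobody noticed. Its list also omits delirium, pressure ulcer and thrombophlebitis.

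The paramedic comparison has a separate gap. A paramedic may make the daily visits, yet no row of the Safety table names the paramedic as a source.

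**Working it through.** **Who sees the patient, and who reports**

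| | Control arm | Remote arm | Named source? |
|---|---|---|---|
| Physician at bedside | daily | only if the physician chooses | yes (MD) |
| Nurse at bedside | shares the minimum of two visits a day | same | yes (RN) |
| Paramedic at bedside | shares the minimum of two visits a day | same | no |

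The asymmetry between randomised arms is therefore confined to the physician.

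**The plan's own figure**

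Inputs from the power section: SD 0.29, margin 0.1, power 80%, alpha 0.025, 105 per arm, or 130 per arm with clustering.

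- Alpha 0.025 one-sided: n = 2 × 0.29² × (1.960 + 0.842)² / 0.1² ≈ 132.0, so 133 per arm. This does not reproduce 105.
- Alpha 0.05 one-sided: 104 per arm (105 with the t distribution), which does reproduce it.

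That mismatch is a separate matter. The illustration below takes the stated 130 per arm and 0.025 as given.

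**Effect of under-detection in the remote arm**

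Inputs and assumptions:

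- True means 0.09 (control) and 0.19 (remote), so the remote arm is exactly at the margin.
- Control-arm detection complete.
- Normal approximation on the difference scale, Poisson variance, clustering ignored.
- Relative detection s in the remote arm is an assumption. The protocol gives no value.

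Share of events that are bedside-observed, from the Appendix table of selected safety data (203 home patients), using only events that are also in the adverse-event list:

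- delirium 5 + pressure ulcer 2 + thrombophlebitis 4 = 11
- transfer back 5
- total 16, so the share is 11/16

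That table does not report falls, hypokalemia or kidney injury, so the share is approximate.

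Formulas:

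- Observed remote mean m = 0.19 × (5/16 + 11/16 × s) if only bedside-observed events are affected, or 0.19 × s if all components are.
- P(non-inferiority) = Φ[(0.1 − (m − 0.09)) / √((m + 0.09)/130) − 1.96]

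Worked case, s = 0.8, bedside-observed events only:

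- m = 0.19 × 0.8625 = 0.1639
- difference = 0.0739
- SE = √(0.2539/130) = 0.0442
- (0.1 − 0.0739)/0.0442 − 1.96 = −1.37, and Φ = 0.086

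| s | Bedside-observed events only | All components |
|---|---|---|
| 1.0 | 2.5% | 2.5% |
| 0.9 | 4.7% | 6.2% |
| 0.8 | 8.6% | 14.0% |
| 0.7 | 14.7% | 28.0% |
| 0.5 | 36.2% | 71.2% |

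With SD 0.29 in each arm instead of Poisson variance, the all-components column gives 7.6% at s = 0.9 and 18.3% at s = 0.8.

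In events: the remote arm at the margin expects 130 × 0.19 = 24.7, of which 24.7 × 11/16 = 17.0 are bedside-observed. Missing 20% of those is about 3.4 events.

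**The case against.** The strongest case against is that the physician is a minor part of detection.

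- A nurse or paramedic is in the home at least twice a day in both arms and facilitates the exam in the remote arm.
- The remote physician still has a daily video contact, with transmitted sounds as needed, and may attend in person.
- Continuous monitoring and daily review of safety data are part of the programme.
- Transfers and deaths are hard to miss, laboratory-defined events do not depend on who is at the bedside, and 30-day mortality comes from a call.
- No document gives a detection rate.

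All of this stands, and it limits the point to a residual risk in the bedside-observed components. It does not remove that risk, because both informants know the arm and one has a different view by design.

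A reader might infer more than the protocol supports, in three ways:

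- That every event arrives only through clinicians whose bedside contact the comparisons vary. The nurse/paramedic visit minimum does not differ between the randomised arms, and the CAM source is the same in both.
- That the paramedic group would be under-detected and so favoured. The paramedic is added to nurse care, and paramedics document in the electronic record, so detection could go either way.
- That paramedic visits lose the delirium component for patients without dementia. The protocol requires a CAM at each visit for dementia patients, but it does not bar paramedics from doing one in others. What is missing is the named source.

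It may also be said that visit forms belong in operational documents. That is fair for the form itself, but the event source is fixed in this protocol's table, and that wording needs the change.

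**Conclusion.** The point holds for the remote vs in-person trial as a moderate, cheaply removed weakness. The protocol relies on unblinded informants whose access differs partly by arm, and any resulting loss in the remote arm favours non-inferiority.

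If the loss is confined to bedside-observed events, 90% or 80% detection takes a nominal 2.5% error to about 5% or 9%. The 6% and 14% for loss across all components are an upper illustration, since several components could hardly be missed. These figures show sensitivity and are not estimates of actual bias. They depend on assumed detection rates, true rates exactly at the margin, and a bedside share taken from an incomplete table.

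For the paramedic comparison the conclusion is narrower: the source list is incomplete, and a detection difference of unknown direction is possible.

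**What to change.** 1. In the Safety table, change the home-patient source to RN or paramedic, plus MD, and make the same change for the CAM.
2. Collect the bedside-observed events (delirium, pressure ulcer, IV-site thrombophlebitis, falls) on the same short form at every nurse or paramedic visit, in both arms.
3. Keep every event in the primary count, whoever detects it, and record who first detected it. Taking physician-only events out of the primary count would be unsound. It would drop real events, including those found when a remote-arm physician chooses to attend in person.
4. Add a sensitivity analysis that excludes events first detected only at an in-person physician visit.
5. For the retrospective paramedic comparison, abstract RN, paramedic and MD notes from the electronic record with one form in both groups.

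Cost: a few minutes per visit, revised table wording and one extra analysis.

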## SUBJECT SELECTION

### Inclusion/exclusion criteria

#### *Inclusion*

- Social
  - Resides within either a 7.5-mile driving radius of the BWFH emergency room
    - Driving radius will be obtained via inputting a nearby (but not exact) address into Google Maps.
  - Has capacity to consent to study OR can assent to study and has proxy who can consent (see subject enrollment, below)
  - Can identify a potential caregiver who agrees to stay with patient for first 24 hours of admission. Caregiver must be competent to call care team if a problem is evident to her/him. After 24 hours, this caregiver should be available for as-needed spot checks on the patient.
    - This criterion may be waived for highly competent patients at the patient and clinician's discretion.
- Clinical
  - $\geq 18$  years old
  - Primary or possible diagnosis of cellulitis, heart failure, complicated urinary tract infection, pneumonia, COPD/asthma, other infection, chronic kidney disease, malignant pain, diabetes and its complications, gout flare, hypertensive urgency, previously diagnosed atrial fibrillation with rapid ventricular response, anticoagulation needs, or a patient who desires only medical management that requires inpatient admission, as determined by the emergency room team.
    - Regarding anticoagulation needs, this includes a patient who requires therapeutic anticoagulation and concomitant monitoring (thus requiring inpatient status)
    - Regarding a patient who desires only medical management, this includes a patient who requires acute care for symptom management, but declines any surgical intervention. This may include a patient who is about to transition to hospice care, for example, but still has the functional capacity to meet our criteria below. Under these circumstances, we would make sure that various contingencies, including possible transition to hospice care or hospital readmission, are completely understood by patients and caregivers as applicable.
    - In order to achieve enrollment goals, we *a priori* reserve the ability to expand this criterion to include patients who fail observation status and patients who

are transferred to the observation unit under the care of the emergency room observation team.

- Regarding IBD
  - Requires intravenous infusion and acute care monitoring per outpatient gastroenterologist
- Regarding acute pancreatitis
  - Please refer to attachment

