### Health Care Utilization

| Measure                                                | Source                                                       | Day(s) Obtained |
|--------------------------------------------------------|--------------------------------------------------------------|-----------------|
| Length of stay, days                                   | RA via MD/RN for home patients; RA EHR review for inpatients | Discharge       |
| IV medication, days                                    | As above.                                                    | Daily           |
| Intravenous fluids, days                               | RA via EHR                                                   | Daily           |
| Intravenous diuretics, days                            | RA via EHR                                                   | Daily           |
| Intravenous antibiotics, days                          | RA via EHR                                                   | Daily           |
| Oxygen requirement, days                               | RA via RN                                                    | Daily           |
| Nebulizer treatment, days                              | RA via EHR                                                   | Daily           |
| Imaging, #                                             | As above. +30 will be cross-checked with Partners data.      | Daily, +30      |
| Lab Orders, #                                          | As above.                                                    | Daily, +30      |
| MD sessions, # of notes                                | As above.                                                    | Daily, +30      |
| Consultant sessions, # of notes                        | As above.                                                    | Daily, +30      |
| PT/OT sessions, # of notes                             | As above.                                                    | Daily, +30      |
| Disposition (routine, SNF, home health, other)         | RA via MD/RN for home patients; RA EHR review for inpatients | Discharge       |
| PCP follow-up within 14 days, y/n                      | RA via pt phone call, cross-checked with Partners data.      | +30             |
| SNF utilization, days                                  | As above.                                                    | +30             |

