**Patient Functional Status and Quality of Life**

| Measure        | Source         | Day(s) Obtained                |
|----------------|----------------|--------------------------------|
| EuroQol -5D-5L | RA via patient | Admission, discharge, +30      |
| SF-1           | RA via patient | -30, admission, discharge, +30 |

|                                                                                                     |                |                                |
|-----------------------------------------------------------------------------------------------------|----------------|--------------------------------|
| Activities of daily living: admission to discharge; admission to 30-day post-discharge              | RA via patient | -30, admission, discharge, +30 |
| Instrumental activities of daily living: admission to discharge; admission to 30-day post-discharge | RA via patient | -30, admission, discharge, +30 |
| Patient Health Questionnaire-2                                                                      | RA via patient | Admission, discharge, +30      |
| PROMIS Emotional Support Short Form 4a                                                              | RA via patient | Admission, discharge, +30      |
| Days at home since discharge                                                                        | RA via patient | +30                            |
| Milestones                                                                                   |                |                                |
| Walk around ward/home                                                                               | RA via RN      | Discharge                      |
| Get to (non-commode) bathroom                                                                       | RA via RN      | Discharge                      |
| Walk 1 flight of stairs                                                                             | RA via RN      | Discharge                      |
| Visit with friends/family                                                                           | RA via patient | Discharge                      |
| Walk outside around my home                                                                         | RA via patient | +30                            |
| Go shopping                                                                                         | RA via patient | +30                            |

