appointment within 7 or 14 days, ability to meet physical milestones after discharge), non-transformed linear regression for normally distributed continuous outcomes (e.g., quality of life scores), log-transformed linear regression for skewed continuous outcomes (e.g., cost), and Cox proportional hazards for time to event outcomes (e.g., time to readmission, time to ED visit). We will use multiple imputation for covariates where data are missing for more than 2% of patients. Lastly, we will perform a limited number of subgroup analyses to determine whether the intervention is more effective in certain patient populations than in others (i.e., effect modification), targeting inadequate health literacy and living alone, for example. We will use interaction terms (e.g., intervention\*characteristic) to determine the statistical significance of effect modification.

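### 30-day mortality rests on a telephone call and days at home on the patient alone, without the records cross-check used for other 30-day outcomes

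*Protocol*

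**What the plan says.** In the Safety table of the protocol, the rows for all-cause and unplanned 30-day mortality each list a single source at day +30: "RA via pt/caregiver call". In the table on functional status and quality of life, "Days at home since discharge" is obtained at +30 by the research assistant from the patient. No caregiver and no record source is listed for that row.

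The Health Care Utilization table treats the same time point differently. PCP follow-up has the source "RA via pt phone call, cross-checked with Partners data". The rows below it (nursing-facility and home health days, readmissions, ED observation stays, ED visits) carry that source forward. Thirty-day cost comes from Partners data.

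Both measures are used. The Summarizing Adverse Events table includes "Mortality (unplanned) 30-day post-discharge", and the section on remote versus in-person care names "days at home since discharge" as a count outcome for Poisson regression.

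**The concern.** Whether these two outcomes are observed can depend on their value. A patient who has died cannot take the call, so a death is recorded only if a caregiver or other contact is reached. The inclusion criteria ask for a caregiver but add: "This criterion may be waived for highly competent patients at the patient and clinician's discretion". Living alone is a recorded covariate and a named subgroup. The criteria also admit some patients close to hospice care, so deaths after discharge are foreseeable. For days at home the listed respondent is the patient alone. The patients with the lowest values are those who died (and cannot answer) and those in a facility (who may be harder to reach).

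The protocol already has a remedy and applies it to an emergency visit but not to a death. The choice of source is made in this table. A later analysis plan cannot recover deaths that were never ascertained.

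**Working it through.** No stated figure depends on these sources, so there is nothing to reproduce. The check has three parts.

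**1. Sources at day +30, side by side (protocol data tables)**

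| Outcome | Call | Partners cross-check listed |
|---|---|---|
| Readmissions, ED visits, ED observation, nursing-facility and home health days | patient | yes |
| All-cause and unplanned 30-day mortality | patient or caregiver | no |
| Days at home | patient | no |

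No other section adds a record source for the last two rows.

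**2. Share of deaths missed**

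Let *u* be the share of patients for whom nobody is reached, and *k* the ratio of death risk in unreached to reached patients. Then share missed = *uk* / ((1 − *u*) + *uk*). The protocol gives neither quantity, so both are assumed.

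| *u* | *k* = 1 | *k* = 3 | *k* = 5 |
|---|---|---|---|
| 5% | 5% | 14% | 21% |
| 10% | 10% | 25% | 36% |
| 20% | 20% | 43% | 56% |

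Example: *u* = 0.10 and *k* = 3 give 0.30 / (0.90 + 0.30) = 25%. Take 130 patients per arm (protocol, Power analysis) and an assumed mortality of 3%. That is 3.9 deaths per arm, of which 3.9 × 0.25 = 0.98 is missed. The rate among the 117 reached is (3.9 − 0.98) / 117 = 2.5%. The loss is 0.98 / 130 = 0.0075 events per patient, against a non-inferiority limit of 0.1. At the extreme of the assumed range (5% mortality, *u* = 20%, *k* = 5) it is 0.05 × 0.556 = 0.028 events per patient.

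**3. Effect on the comparison**

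Let *q* be true mortality and *c* the share of deaths for which a respondent is reached, with 90% of survivors reached (all assumed). The rate among those reached is *qc* / (*qc* + (1 − *q*) × 0.9).

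| *c* (same in both arms) | True 2% reads | True 4% reads | Risk difference (true 2.0 points) |
|---|---|---|---|
| 0.4 | 0.90% | 1.82% | 0.92 |
| 0.6 | 1.34% | 2.70% | 1.36 |
| 0.8 | 1.78% | 3.57% | 1.79 |

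The rates lose about 11% to 55% of their value, and the risk difference shrinks with them. The odds ratio does not. The odds among those reached are *qc* / ((1 − *q*) × 0.9), and with equal reach in both arms *c* and 0.9 cancel. The true odds ratio is (0.04/0.96) / (0.02/0.98) = 2.04. At *c* = 0.4 the observed one is (0.016/0.864) / (0.008/0.882) = 2.04.

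The odds ratio moves only if relative reach differs by arm. If *c* were 0.4 in the 4% arm and 0.8 in the 2% arm, it would be 2.04 × 0.4/0.8 = 1.02. Nothing in the protocol indicates such a difference.

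**The case against.** The strongest case against is that the mortality rows name the caregiver, which covers the situation in which the patient cannot answer. The caregiver criterion is waivable only for highly competent patients. It concerns presence in the first 24 hours and later spot checks, so a waiver does not mean that no contact exists. Caregiver burden is also collected from the caregiver at +30, which implies a second contact at that time. A death during a readmission within Partners would probably surface when readmissions and cost are checked. All of this stands for mortality. It narrows the gap to deaths with no reachable contact that do not surface in those other checks. It does not help days at home, whose row lists no caregiver.

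The reach and mortality figures above are assumptions, and the rate among those reached presumes that unreached patients leave the denominator, which the protocol does not state.

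Three stronger readings are tempting, and the documents do not support them:

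- *Missed deaths pull the comparison toward no difference.* The protocol specifies logistic regression for binary outcomes, and with equal reach across arms the odds ratio is preserved. Only absolute rates and differences shrink.
- *The non-inferiority result is compromised.* The primary outcome is worded as "number of adverse events during the acute episode of care", while the table it cites lists a post-discharge death. The two need reconciling. Even if such deaths count, the illustrated loss is small against the limit.
- *The missing-data plan ignores these outcomes.* The protocol says "We will use multiple imputation for covariates where data are missing for more than 2% of patients", but handling of missing outcomes is commonly left to the analysis plan, which is not at hand. Its absence here is not a fault.

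**Conclusion.** The point holds as a correctable weakness in ascertainment. Two outcomes that are most likely to be unobserved when they are worst lack the cross-check given to their neighbours. Absolute 30-day mortality and risk differences between arms would be understated and days at home overstated. Bias in the mortality odds ratio requires reach of the deceased relative to survivors to differ by arm.

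The amount is not known. Over assumed unreached shares of 5% to 20% and death-risk ratios of 1 to 5, between 5% and 56% of deaths would be missed, and how well the caregiver call works decides where in that range the trial falls. In the example above the effect on the adverse-event count is about 0.0075 per patient, so the non-inferiority decision is unlikely to change for this reason alone. The harm falls on the mortality and days-at-home results themselves.

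**What to change.** In the Safety table, change the source of both 30-day mortality rows to: *pt/caregiver call, cross-checked with Partners data (EHR vital status)*.

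In the functional status table, derive days at home from the discharge, readmission, nursing-facility and death dates or days, counting zero days after death, and keep the patient or caregiver call as a supplement. Readmission dates and nursing-facility days are already collected with the cross-check. The end date of each readmission would need to be abstracted with them.

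The cost is minor abstraction time in a source already used at +30. Deaths outside the Partners system may still be missed. A public death-record search for patients whose status stays unresolved is an optional addition with some further effort.
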